#### 9.2.5.2. Subgroup analysis

We will use stratified analysis to assess to what extent the effect of the intervention on the primary outcome is influenced by the following potential effect modifiers:

##### *Demographic modifiers*

1. Age: Infants vs older children. PMC is hypothesized to be more effective in older children based on results from the previous trial in Malawi.
2. Socio-economic and/or educational status: Quintiles based on SES-index rank score. PMC is hypothesized to be more effective in children from poorer and less educated households as they may have more, and more severe post-discharge events because of barriers resulting in delays in seeking appropriate care.
3. Distance to nearest study clinic: terciles. Distance from health facilities has been associated with increased mortality, and can interfere with event capture.

##### *Clinical modifiers*

4. Syndrome on admission: non-malaria severe anaemia vs severe malaria anaemia. PMC is hypothesized to be more effective in children with severe malaria anaemia on enrolment as they represent a selected subgroup that is more exposed to malaria for environmental, behavioural or host-genetic reasons.
5. HIV status: HIV-infected vs HIV-uninfected. PMC is hypothesized to be more effective in HIV uninfected children as HIV-infected children may have high rates of readmissions due to other causes and may benefit from antimalarial prophylactic properties of daily cotrimoxazole.
6. Hb on randomization: Terciles. PMC is hypothesized to be more effective in children with the lowest Hb as they may be at highest risk of rebound severe anaemia without an intervention.
7. Previous hospital admittance: lowest 50% vs highest 50%. PMC is hypothesized to be more effective in children with a history of previous admissions as they represent a selected subgroup at highest risk of severe anaemia or malaria for environmental, behavioural or host-genetic reasons.

##### *Transmission variables*

8. Malaria transmission intensity: moderate vs high. PMC is hypothesized to be more effective in children living in high transmission areas as the relative contribution of malaria to post-discharge morbidity may be higher and thus more malaria related events can be prevented.
9. Residence: Urban vs rural. PMC is hypothesized to be more effective in children living in rural areas which have higher malaria transmission.
10. Season: Terciles, based on average rainfall during the 6 month study period for each child. PMC is hypothesized to be more effective in malaria transmission season when more potential malaria related events can be prevented.
11. ITN use vs non-use. PMC is hypothesized to be more effective in non ITN users as more potential malaria related events can be prevented.

12. Study Site: about 7 sites, as used in the stratification. PMC is hypothesized to be more effective in children living in high transmission sites as the relative contribution of malaria to post-discharge morbidity may be higher and thus more malaria related events can be prevented.

#### *Intervention modifiers and time of assessment*

13. Period of assessment: extended follow-up period 15-26 weeks vs PMC period 2-14 weeks. PMC is hypothesized to be much more effective during the PMC period when drug levels remain above the minimum inhibitory concentrations.
14. Dose in mg/kg received: Terciles. It is hypothesized that variations in dose received in mg/kg due to natural variation in bodyweight within the fixed weight bands, are small and will not affect efficacy.

Because the study is not designed to have sufficient power for subgroup analysis, we will interpret the results of subgroup analysis cautiously. No adjustment will be made for multiple comparisons.

#### *9.2.5.3. Sensitivity analysis*

A number of sensitivity analyses will be conducted to assess the robustness of the primary endpoint analysis. These include un-stratified Poisson regression models, analysis of the per-protocol subject population, and covariate adjusted analysis. Other regression methods including negative binomial regression and models for recurrent event time data will also be explored. Additional post-hoc analyses may also be conducted if deemed necessary. In addition, the results of the statistical models with and without imputation for missing values for co-variables values will be compared. Covariates for co-variate adjusted analysis and subgroup analysis, and alternative statistical models, which will be specified in the statistical analysis plan (SAP).

#### *9.2.6. Analysis of adverse events*

Adverse reactions will be reported and tabulated for each treatment arm, overall and per body system and adverse event, on an intention to treat basis. Treatment emergent adverse events are defined as adverse events that had an onset day on or after the day of the first dose of study medication. Adverse events that have missing onset dates will be considered to be treatment emergent. No formal statistical testing will be undertaken. All laboratory data will be listed.

## **9.3. PROCEDURES FOR ASSESSING EFFICACY PARAMETERS**

### *9.3.1. Primary outcome*

*All-cause mortality* will be assessed during the visits at 2, 6, and 10 weeks to administer PMC and the end of study visit at 6 months.

*All-cause and disease specific re-admissions* will be assessed through passive case detection and through a questionnaire administered during the visits at 2, 6, 10 weeks and 6 months. Details of the admission and treatment provided will be recorded, where available, on special study forms including RDT or malaria smear results and use of antimalarials, to allow for differentiation between malaria, severe anaemia, and other syndromes.

### 9.3.2. Secondary outcomes

*All-cause and malaria specific clinic visits* will be assessed through passive case detection and through questionnaires administered during the visits at 2, 6, 10 weeks and 6 months. In order to facilitate passive surveillance, all participants will be provided with unique study ID card for identification of study participants during unscheduled visits to outpatient departments or hospitals. Caretakers will be encouraged to seek care from the study clinics. Details of clinic visits will be recorded on special study forms including RDT or malaria smear results to allow for differentiation between malaria and non-malaria clinic visits.

## 9.4. LABORATORY METHODS

### 9.4.1. Techniques for host and parasite genetic assays

Sample aliquots or DNA aliquots will be sent to the laboratories of [name], University of Massachusetts, and [name], University of North Carolina, allowing for efficient well-controlled and cost-effective genetic analysis. We will be using deep sequencing techniques using massively parallel sequencing with which both [name] and [name] laboratories have extensive experience in terms of all laboratory and computational aspects. High-throughput sequencing allows for the rapid analysis of multiple loci and multiple samples. Molecular Inversion Probe techniques will be used that will allow the testing of multiple loci for each participant within a single tube and batch analysis of hundreds of participants within a single sequencing run. A strength of molecular inversion probes is that it affords single tube testing per sample for a panel of genes and allows for the rapid addition of additional genes as they are discovered, which is important given the ongoing concern about artemisinin resistance in Asia and Africa. A comprehensive panel for all known drug resistance loci in *P. Falciparum* developed in the laboratory of [name] (unpublished) will be used for the parasite genetics.

Because the high-throughput sequencing techniques are most amenable to being able to batch hundreds of samples (if not thousands) at a time, we expect to perform the majority of the analysis towards the end of the field work when all or the majority of the samples have been collected in order to provide cost-effective and well controlled analysis.

## 9.5. MONITORING

### 9.5.1. Data Monitoring

#### 9.5.1.1. Data Monitoring and Ethics Committee (DMEC)

Since the study is a clinical trial in a potentially vulnerable patient population, an independent Data Monitoring and Ethics Committee (DMEC) will be set up. The DMEC will be critical to ensure that the subjects are protected from harm, while also ensuring that the study integrity is not compromised. The DMEC will consist of 3 or 4 independent members knowledgeable in the conduct of clinical trials. They will meet regularly (e.g. twice yearly or more frequent if so required) during data collection period to provide a review of blinded (and if requested unblinded) data to ensure the safety, rights and well-being of trial participants. The trial statistician could also be asked to attend the meetings. The role and membership of the DMEC is described in more detail in Appendix III. Terms of Reference Oversight committees, page 113.

#### 9.5.1.2. Interim analyses and criteria for termination of the trial

An interim analysis will be conducted on the primary endpoint when 50% of participants have completed the 6 months follow-up. The interim-analysis will be performed by an independent statistician, blinded for the treatment allocation. The statistician will report to the independent DMEC. The DMEC will have unblinded access to all data and will discuss or report the results of the interim-analysis with the Trial Steering Committee (TSC), e.g. in a joint meeting. The TSC decides on the continuation of the trial and will report to the ethics committees.

The Lan-DeMets spending function with O'Brien-Fleming type boundaries will be employed and the sample size inflated (see 8.8.1, page 40) to preserve the overall one-sided type I error rate for efficacy at the  $\alpha=0.05$  level at the final analysis. If the stopping boundary is crossed at the interim analysis and the RR is less than 1, i.e. the observed incidence rate in the PMC arm is less than the expected incidence rate under the null hypothesis, it will be concluded that the study has demonstrated that the efficacy of PMC is superior to that of placebo in the prevention of death or all-cause readmission. The trial recruitment can then be stopped unless the DMEC advises otherwise. Statistics will not be the sole basis for the decision to stop or continue and the DMEC can advise to continue recruiting in the trial, or stop recruiting but continue to complete the intervention as per randomization in the remaining active children, even if statistically the stopping boundary is crossed, e.g. in order to continue collecting more safety information or data for further sub-group analyses etc. The trial will not be stopped in case of futility, unless the DMEC during the course of safety monitoring advises otherwise.

A detailed plan for interim analysis, the provisional stopping rules and how the stopping rules will be applied, will be drawn up prior to the start of the interim analysis and documented in the study statistical analysis plan.

In addition, regular review of the quality of the study data will be conducted at each meeting of the DMEC.

The sponsor reserves the right to temporarily suspend or prematurely discontinue this study at any time for reasons including, but not limited to, safety or ethical issues or severe non-compliance. If the sponsor determines such action is needed, it will discuss this with the investigator. When feasible, the sponsor will provide advance notification to the investigator of the impending action prior to it taking effect. The sponsor will promptly inform the IEC/IRB and provide the reason for the suspension or termination.

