## **8.8. SAMPLE SIZE**

### *8.8.1. Trial*

#### *8.8.1.1. Sample size re-estimation*

Following recommendations from the DMEC and TSC, a blinded interim sample size re-estimation was conducted to take the lower than expected rate of loss to follow-up into account and the higher than expected pooled event rate of the composite primary endpoint (death or all-cause readmission) across both arms. This was favoured over an interim analysis, because the available funding did not allow and extension of the recruitment period, even if the results of any interim analysis would suggest this was required.

The revised sample size calculations were conducted in PASS (v15) software using a tests for the ratio of two Poisson rates. A total sample size of 1040 children (520 per arm) is required to detect a 25% reduction in the incidence of the composite primary outcome from 1,152 per 1000 child years (530 events per 1000 children during the 24 weeks from randomization at 2 weeks to the end of follow-up at 26 weeks) in the control arm to 864 per 1000 child years (398 per 1000 children over 24 weeks) in the intervention arm (power 80%,  $\alpha=0.05$ ), allowing for 10% loss to follow-up. The same

sample size would also provide 90% power to detect a 28.7% reduction in the primary endpoint from 1,152 to 822 events per 1000 children years.

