#### 8.8.1.2. Original sample size estimation

Sample size calculations were conducted using EAST (v6.2) Software. The total sample size will be 2212 children (1106 per arm) across both countries pooled. A sample size of 1858 is required to allow detection of a 30% reduction in the mean incidence rate (incidence density) of the composite primary outcome (death or all-cause readmission) from 469 per 1000 child years (216 events per 1000 children during the 24 weeks from randomization at 2 weeks to the end of follow-up at 26 weeks) in the control arm to 328 per 1000 child years (151 per 1000 children over 24 weeks) in the intervention arm (power 90%,  $\alpha=0.05$ ). A single child can have multiple (repeated) primary events. 1865 children are required to allow for 1 interim analysis using the Lan-DeMets spending function with O'Brien-Fleming type boundaries to preserve the overall two-sided type I error rate for efficacy (see 9.5.1.2, page 49). To allow for 15.7% loss to follow-up a total of 2212 children will be conducted.

The impact estimate of 30% is based on the previous trial in Malawi where the protective efficacy (PE) with monthly AL was 30% (and 31% for death or admission for malaria or anaemia). The incidence rate of 469 per 1000 child years is the average incidence rate observed during the 2-26 weeks post-discharge period in the control arm in the previous trial in Malawi (536 per 1000 child years) and the rate in western Kenya in 2013 (402 per 1000 child years). The estimated rate of loss to follow of 15.7% is conservative and three times the rate observed in our previous studies that involved 6 months follow-up of children admitted for severe malaria or severe anaemia: this was 7.4% in the earlier IPTpd/PMC trial in Malawi across 4 hospitals, and 3.5% and 5.0% in two previous observational studies in Uganda. However the study will involve a total of 7 hospitals, only 3 of which are experienced research hospitals. We have therefore allowed for 15.7% loss to follow-up, which is the average of 10% in the 3 experienced sites and 20% in the remaining 4 sites.

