### *9.2.5. Assessment of efficacy*

#### *9.2.5.1. Primary analysis*

Primary analysis will be by intention to treat, and include all primary endpoint events to capture the potential effect of PMC on reducing first and repeat events. The associated statistical null hypothesis is that there is no difference between the treatment groups in the distribution of the incidence rate of the primary endpoint, and the alternative hypothesis is that there is a difference between treatment groups.

The follow-up time will be measured as the time in days from the date of randomisation to the end of follow-up, death or drop-out. The incidence rate will be calculated per arm and the rate ratio (RR, PMC to placebo) and 95% confidence intervals (CI) estimated using Poisson regression models, stratified by country, with treatment (as randomized) as the only co-variate. The results will be expressed as the relative rate reduction (RRR) (95% CI) calculated as 100 multiplied by (1–RR).

In addition to the final analysis, the primary statistical hypothesis will be tested in an interim analysis when approximately half of patients are recruited as described in more detail in section 9.5.1.2, page 49.

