## **10. TIMEFRAME AND DURATION OF THE STUDY**

The total duration of the study is 4 years, including 12 months of study preparation, approximately 30 months of field work and 6 months of data analysis and report writing. The study will include 1 interim analysis of safety data when 50% of the patients have completed 26 weeks follow-up.

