##### *Trial members*

- The Chief Investigator and all Country Co-Principal Investigators.
- Other co-investigators and the trial statistician will attend the meetings if and when required.

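### The protocol says the interim analysis was set aside yet still orders an efficacy interim, and 9.5.1.2 sets its error rate at one-sided 0.05 against two-sided 0.05 elsewhere

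*Protocol*

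**What the plan says.** **Whether there is an efficacy interim.** Section 8.8.1.1, on the blinded re-estimation that led to 1040 children, says: "This was favoured over an interim analysis, because the available funding did not allow and extension of the recruitment period". Three other current sections still plan an interim:

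- 9.2.5.1: "the primary statistical hypothesis will be tested in an interim analysis when approximately half of patients are recruited". It refers to 9.5.1.2 for details.
- 9.5.1.2: "An interim analysis will be conducted on the primary endpoint when 50% of participants have completed the 6 months follow-up". A Lan-DeMets O'Brien-Fleming boundary follows; crossing it with a rate ratio below 1 establishes superiority of PMC.
- Section 10: "The study will include 1 interim analysis of safety data when 50% of the patients have completed 26 weeks follow-up".

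**At what error rate.** Section 9.5.1.2 uses the boundary "to preserve the overall one-sided type I error rate for efficacy at the" 0.05 level, and points to 8.8.1 for the matching inflation of the sample size. There, 8.8.1.2 describes the same boundary as chosen "to preserve the overall two-sided type I error rate for efficacy". Section 8.8.1.1 gives alpha 0.05 without saying how many sides. Section 9.2.5.1 has a non-directional alternative and a 95% confidence interval.

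**Who hears the result.** In 9.5.1.2 the unblinded DMEC "will discuss or report the results of the interim-analysis with the Trial Steering Committee (TSC"). The TSC's trial members are "The Chief Investigator and all Country Co-Principal Investigators". Section 16.3.3.2 reserves results by treatment group for the DMEC.

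**The concern.** Two things that define the trial's decision rule are stated in conflicting ways: whether the primary hypothesis is tested once or twice, and how much one-directional error is allowed. The first decides whether the trial can stop early for benefit and whether the final critical value needs adjusting. The second matters more, because a final Z between about 1.66 and 1.96 would be a success under 9.5.1.2 and a failure under 9.2.5.1. The trial is meant to inform a WHO recommendation (7.1), so its conclusion should not depend on which section is read.

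A likely cause is incomplete editing. The change log for Amendment 4.0 lists only pages 10, 14, 21 and 40, while the interim text stands on about pages 45 to 49.

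**Working it through.** **1. Which sidedness was the interim design built on?** Reproduce the only sample size that includes the interim (8.8.1.2: 1858 without interim, 1865 with one, 2212 after loss). Inputs: rates 0.469 and 0.328 per child-year, 24 weeks, power 90%, alpha 0.05, 1:1.

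n per arm = (z_alpha + z_power)² × [1/(λ1·t) + 1/(λ2·t)] / [ln(λ2/λ1)]², with t = 24/52 = 0.4615.

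- 1/(0.469 × 0.4615) + 1/(0.328 × 0.4615) = 4.620 + 6.606 = 11.226; [ln(0.328/0.469)]² = 0.1279.
- Two-sided: (1.960 + 1.282)² = 10.51, so n = 922.4, total 1846 (1852 with t = 0.46). Stated: 1858.
- One-sided: (1.645 + 1.282)² = 8.56, so n = 751.8, total 1504 (1510 with t = 0.46).
- Inflation for one O'Brien-Fleming look at half information: factor 1.0034 two-sided, 1858 × 1.0034 = 1864.4 (stated 1865); factor 1.0072 one-sided, 1858 × 1.0072 = 1871.4.
- 1865 / (1 − 0.157) = 2212.3. Stated: 2212.

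Both the base number and the 7-child increment fit two-sided 5% only. The one-sided wording in 9.5.1.2 therefore contradicts the calculation it relies on.

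**2. What thresholds follow?** Spending function at information fraction t, with one-directional tail a: a(t) = 2[1 − Φ(z_{1−a/2}/√t)]. The interim bound c1 is the normal quantile at 1 − a(t). The final bound c2 solves P(Z1 ≥ c1 or Z2 ≥ c2) = a, with correlation √t.

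| Reading | a | t | spent | interim Z | final Z |
|---|---|---|---|---|---|
| No efficacy interim, two-sided 0.05 | 0.025 | – | – | – | 1.960 |
| Interim, two-sided 0.05 | 0.025 | 0.50 | 0.00153 | 2.963 | 1.969 |
| Interim, two-sided 0.05 | 0.025 | 0.60 | 0.00381 | 2.669 | 1.981 |
| Interim, one-sided 0.05 (9.5.1.2) | 0.05 | 0.50 | 0.00557 | 2.538 | 1.662 |

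A final Z of 1.662 is a two-sided p of 0.0965. Stopping at the interim would need a one-sided p of 0.0056 instead of 0.0015. The chance of a false claim of benefit is 5% instead of 2.5%.

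**3. What does this mean for the rate ratio?** With 10% loss, 520 × 0.9 = 468 per arm. At the planned rates the expected events are 468 × (1.152 + 0.864) × 24/52 = 435. With SE(log RR) ≈ 2/√435 = 0.096, the largest rate ratio that counts as success at the end is exp(−1.960 × 0.096) = 0.83 two-sided and exp(−1.662 × 0.096) = 0.85 one-sided.

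**4. What does the interim itself cost?** Little. One two-sided look at half information followed by an unadjusted 1.960 gives a total two-sided error of about 5.1%. The conflict over sides drives the difference.

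**5. Do the two efficacy timings agree?** No. Assume uniform enrolment over the 24 months of 8.9 and a constant event rate. Half are recruited at month 12: a quarter have completed 6 months and another quarter are on average halfway, so information is about 0.25 + 0.25/2 = 0.375. Half have completed 6 months at month 18, when three quarters are recruited; information is about 0.50 + 0.25/2 = 0.625 if partial follow-up counts, and 0.50 if only completers count.

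**The case against.** The strongest reply is that the SAP will settle this. Section 9.5.1.2 requires the interim plan and stopping rules to be written before the interim, 9.2 lets the SAP supersede the protocol and requires it before unblinding, and 8.10.2 discloses allocations only after data lock and submission of a SAP to the DMEC. That stands against one tempting inference, that the threshold would be chosen after seeing the results; the documents do not support it. It does not remove the contradiction, because the protocol itself fixes an error rate and orders a test that it elsewhere says was set aside.

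It can also be said that the one-sided wording looks like a single slip, since the final test in 9.2.5.1 is clear, and that it governs nothing if the interim is dropped. Both are fair and make the correction easy. However, 8.8.1.1 says only that re-estimation was favoured; it nowhere cancels the interim, so 9.5.1.2 remains in force as written.

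Other inferences go too far:

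- *Three efficacy interims are ordered.* Section 10 describes safety data, and 9.2.5.1 defers to 9.5.1.2. There is one efficacy interim with two timings, and a third section that gives the single interim a different purpose.
- *The current sample size section says two-sided.* The words stand only in the retained original estimation, 8.8.1.2. In 9.2.5.1 two-sidedness follows from the alternative and the interval.
- *1040 is short because it has no interim allowance.* A factor of 1.0037 (two-sided, 80% power) is about 4 children in 1040, and the omission fits a plan without an interim.
- *Investigators will see results by arm.* Section 9.5.1.2 does not say by arm, 16.3.3.2 restricts such results to the DMEC, 16.3.3.3 has the DMEC report a recommendation, and 16.3.2.3 makes the TSC majority independent. The wording leaves room for disclosure but does not order it.

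**Conclusion.** The point holds as an internal contradiction that needs correcting. The protocol both sets aside and orders an efficacy interim, and its only explicit boundary is attached to a one-sided 0.05 error that disagrees with its source calculation and with the primary analysis. Taken literally, 9.5.1.2 doubles the allowed rate of false claims of benefit, from 2.5% to 5%, and lowers the final critical Z from 1.96–1.97 to about 1.66. In rate-ratio terms the bar moves from about 0.83 to 0.85. The Z values assume an information fraction of 0.5; the rate ratios also assume the planned event rates, Poisson variation and 10% loss. The status of the interim matters less for error control (1.960 against 1.969), but it decides whether the trial may stop early for efficacy. The SAP, not available here, may already resolve both.

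**What to change.** - In 9.2.5.1 and 9.5.1.2, delete the efficacy interim with its boundary and inflation text, in line with 8.8.1.1. Keep the safety review of Section 10. State that the final test of the primary endpoint is two-sided at 0.05.
- If an efficacy look is kept, amend 8.8.1.1 and Section 10 to say so. Give one timing, and specify a Lan-DeMets O'Brien-Fleming boundary at overall two-sided 0.05, computed at the information fraction actually observed (for example 2.963/1.969 at 0.50 and 2.669/1.981 at 0.60). Do not fix the critical values in advance.
- Align the reporting sentence in 9.5.1.2 with 16.3.3.2 and 16.3.3.3: the DMEC passes a recommendation to the TSC, and results by arm stay with the DMEC.

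The cost is a wording amendment, made before any unblinded comparison; no change to sample size or procedures is needed. The downside is a stricter threshold than the one-sided text would give.
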